### Study Setting and Participants

This study focuses on school-aged children in Haidian District, Beijing, and includes a 3-year prospective follow-up. As the educational and technological hub of northwest Beijing, Haidian District has a well-established education management system, facilitating research coordination. Furthermore, the high level of parental compliance with myopia prevention measures in the region ensures the successful implementation of long-term follow-up.

Infants typically exhibit a hyperopia of +3.0 to +4.0 D, which transitions into a period of rapid development before the age of 3 years, followed by a slower developmental phase. By approximately 12 years, the process of emmetropization is gradually completed. On the basis of this developmental pattern, this study focuses on school-aged children as the target population. For this study, children aged 6 to 9 years who met the eligibility criteria were invited to continue annual follow-up examinations for an additional 3 years. Figure 1 illustrates the overall participant flow, including cohort enrollment, eligibility assessment, annual follow-up visits, and identification of incident myopia cases for nested case-control analyses. Textbox 1 lists the inclusion and exclusion criteria.

**Figure 1. F1:**
[figure not shown]
Flowchart of the study.

Textbox 1.Inclusion and exclusion criteria.
**Inclusion criteria**
Children aged 6 to 9 years, regardless of sexAbility to cooperate during examinationsParental consent obtained through signed informed consent
**Exclusion criteria**
Children with a history of drug allergiesChildren with heart disease, cranial trauma, epilepsy, Down syndrome, or glaucomaChildren with a history of myopia prevention interventions (eg, atropine or peripheral defocus corrective lenses)

### Sample Size Calculation

The sample size was estimated based on the planned analyses of incident myopia over the 3-year follow-up in the prospective cohort, with prespecified 1:1 matching in the nested case-control component. Published epidemiological studies indicate that myopia prevalence is relatively low in preschool-aged children but increases rapidly after school entry. For example, Lan et al [18] reported that the prevalence of myopia among 3-year-old children was <2.5%, whereas He et al [19] reported a prevalence of 5.9% among 6-year-old children and an average prevalence of approximately 36% among primary school students in Guangzhou.

On the basis of these data and the anticipated number of incident myopia cases during follow-up, the minimum required cohort size was estimated to be 915 participants to support multivariable analyses and the prespecified nested case-control comparisons. Allowing for an anticipated 10% loss to follow-up, the final target sample size was increased to 1006 participants. This cohort size is expected to generate a sufficient number of incident myopia cases during follow-up to allow for 1:1 risk-set matching and adjustment for key confounders.

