### Outcome Measures

#### Primary Outcome

The primary outcome is incident myopia, defined as the development of myopia during follow-up among participants who were nonmyopic at baseline. Myopia is defined as a spherical equivalent refraction (sphere +1/2 cylinder) of ≤−0.50 D in either eye under cycloplegia [20].

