#### Secondary Outcomes

The secondary outcomes assessed in this study include the following:

Prevalence of myopia at baseline and each annual follow-up visit [4]Annual change in AL [21]Annual change in ACD [22]Annual change in CR [23]Annual change in the AL to CR ratio [23]

All outcomes are assessed annually throughout the 3-year follow-up period using standardized protocols.

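### The target of 1006 keeps about 905 children after 10% loss, not the stated minimum of 915, and the plan does not say whether 915 counts children already myopic at baseline

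*Protocol article*

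**What the plan says.** The Sample Size Calculation section of the protocol article gives the requirement as follows: "the minimum required cohort size was estimated to be 915 participants to support multivariable analyses and the prespecified nested case-control comparisons". The stated basis is a set of published prevalences together with an expected case count: "On the basis of these data and the anticipated number of incident myopia cases during follow-up". That case count is not given. The section then makes one adjustment: "Allowing for an anticipated 10% loss to follow-up, the final target sample size was increased to 1006 participants".

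Three other sections determine which children can contribute:

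- **Primary Outcome.** Incident myopia is "defined as the development of myopia during follow-up among participants who were nonmyopic at baseline". The Study Design section adds that each control is drawn from cohort members still at risk at the same time point as the case.
- **Textbox 1.** The inclusion list opens with "Children aged 6 to 9 years" and contains no refractive criterion. The only myopia-related exclusion is previous preventive intervention, such as atropine or defocus lenses. Existing myopia is not listed.
- **Secondary Outcomes.** The first item is "Prevalence of myopia at baseline and each annual follow-up visit", so some children are expected to be myopic at baseline.

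**The concern.** There are two separate issues.

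The first is arithmetic. To be left with N after a proportion d is lost, one recruits N/(1 − d). Multiplying by (1 + d) always falls slightly short. Because the section calls 915 a minimum, the target should deliver it under the section's own loss assumption.

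The second is the denominator. A child myopic at baseline can be neither a case nor a control in the nested case-control analysis. If such children are enrolled and counted towards 1006, the cohort at risk for the primary outcome is smaller than the headline figure. Loss to follow-up is the only adjustment the section states. At stake is whether a reader can tell how many children the primary analysis is expected to draw on.

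**Working it through.** **Inputs.**

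- Minimum cohort 915, loss 10%, target 1006 (Sample Size Calculation).
- Prevalence of myopia 5.9% at age 6 (same section, from a cited study).
- Baseline prevalences of 10% and 15% are my assumptions. They are included because eligibility runs to age 9 and the section says prevalence rises quickly after school entry.

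**Step 1. Reproduce the stated target.** 915 × 1.10 = 1006.5, which truncates to 1006. The plan's figure is therefore reproduced by multiplication. Even on that method, rounding up would give 1007.

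**Step 2. Apply the plan's own loss rate.** 1006 × 0.90 = 905.4, so about 905 remain. The shortfall is 915 − 905 = 10 children, and 10/915 = 1.1%.

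**Step 3. Inflate by division.** 915/0.90 = 1016.7, rounded up to 1017. Check: 1017 × 0.90 = 915.3. The difference from the stated target is 11 children, and 11/1006 = 1.1%.

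**Step 4. Loss rate at which 1006 suffices.** 1 − 915/1006 = 9.05%. The target meets the minimum only if loss is no more than about 9%.

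**Step 5. Baseline myopia, on the condition that 915 means children at risk.** With baseline prevalence p, the nonmyopic completers from 1006 enrolled number 1006 × 0.90 × (1 − p). The enrolment needed for 915 of them is 915/(0.90 × (1 − p)).

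| Baseline myopia p | Source | Nonmyopic completers from 1006 | Shortfall against 915 | Enrolment needed |
|---|---|---|---|---|
| 5.9% | cited, age 6 | 905.4 × 0.941 = 852 | 63 (6.9%) | 915/0.8469 = 1080.4, so 1081 |
| 10% | assumed | 905.4 × 0.90 = 815 | 100 (10.9%) | 915/0.81 = 1129.6, so 1130 |
| 15% | assumed | 905.4 × 0.85 = 770 | 145 (15.8%) | 915/0.765 = 1196.1, so 1197 |

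**Step 6. What cannot be checked.** The 915 itself cannot be re-derived, because the article gives no power, effect size, exposure prevalence or case count. A condensed article may leave these to the full protocol, and I do not count their absence as a fault. It does mean that the condition in Step 5 can be neither confirmed nor ruled out.

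**The case against.** **The attrition gap is trivial.** It is 10 or 11 children, about 1%. Both 915 and the 10% are estimates, and a loss of 9% instead of 10% closes the gap. This stands as an argument about severity: no conclusion of the study turns on it. It does not make the stated figures agree.

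**Lost children are not wholly lost.** Cases are identified at each annual visit, and controls come from those still at risk at that visit. A child who drops out after year 1 or 2 can already have served as a case or a control. This stands. The counts in Steps 2 and 5 treat every lost child as contributing nothing, so they are the worst case.

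**The 915 may already allow for baseline myopia.** It is described as a cohort size, worked out partly from an anticipated number of incident cases, and the 5.9% at age 6 is among the figures cited. The Introduction also describes the cohort as one of children with physiological hyperopia, although the listed criteria do not enforce this. This stands too. A reader might infer that baseline-myopic children were overlooked in the calculation, but the document shows only that no allowance is stated.

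**The average of about 36% should not be used as a baseline rate.** A reader might apply it and conclude that the at-risk cohort falls more than a third below 915. The article gives that figure as an average across primary school students, not for children entering at 6 to 9 years. The exclusion of children with earlier preventive treatment may lower baseline myopia further. That scenario is not supported.

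**Conclusion.** The point holds in two parts, and its severity is minor.

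The first part is certain. On the plan's own figures the target does not deliver the stated minimum: about 905 against 915, where division gives 1017. The size is about 1%.

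The second part is an ambiguity that needs reconciling, not a demonstrated error. Eligibility admits baseline-myopic children, the primary analysis cannot use them, and the Sample Size Calculation section does not say which group 915 counts.

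- If 915 counts all enrolled children, only the 1% arithmetic correction applies to the target, and the number at risk is simply unstated.
- If it counts children at risk, the shortfall is about 7% at the cited 5.9%, and about 11% to 16% at an assumed 10% to 15%.

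The second branch rests on three assumptions: that meaning of 915, the cited rate carrying over to this cohort, and lost children contributing nothing.

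A reader might also infer that the source cohort of 2109 can readily supply a larger sample. The article does not say how many of those children remain in contact, are eligible or have consented, so this cannot be assumed.

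**What to change.** 1. Correct 1006 to 1017, or keep 1006 and state that about 905 children are expected to be retained.
2. Add one sentence saying whether 915 counts enrolled children or children nonmyopic at baseline, and reconcile it with Textbox 1. Only the investigators can say which is meant.
3. If 915 means nonmyopic children, name the assumed baseline prevalence. Then either restate the target (about 1081 at 5.9%; 1130 to 1197 at 10% to 15%) or keep the target and state the expected at-risk number. If completers are quoted, note that children lost after an early visit still contribute to earlier risk sets.

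The cost is one corrected figure and a sentence or two. The only downside is a slightly less favourable stated number. The design and the planned analyses do not change.

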### Outcome Measures

#### Primary Outcome

The primary outcome is incident myopia, defined as the development of myopia during follow-up among participants who were nonmyopic at baseline. Myopia is defined as a spherical equivalent refraction (sphere +1/2 cylinder) of ≤−0.50 D in either eye under cycloplegia [20].

#### Secondary Outcomes

The secondary outcomes assessed in this study include the following:

Prevalence of myopia at baseline and each annual follow-up visit [4]Annual change in AL [21]Annual change in ACD [22]Annual change in CR [23]Annual change in the AL to CR ratio [23]

All outcomes are assessed annually throughout the 3-year follow-up period using standardized protocols.

### Examinations

Parameters measured included cycloplegic refraction, recording of refractive changes, visual acuity, postdilated refraction, AL, ACD, CR, eye position, fundus, height, and weight.

All the abovementioned metrics were collected at each follow-up visit, and data were collected annually for a specified period.

### Questionnaires

#### General Information Questionnaire

Participants’ general information was collected, including name, sex, gestational age at birth, mode of delivery, birth weight, whether the parents were myopic, the degree of myopia, and the health of the mother during pregnancy.

#### Myopia-Related Genetic and Environmental Factors Questionnaire

These data were collected using Children’s Myopia-Related Factors Questionnaire, which parents completed by scanning the QR code; the questionnaire includes past history, family history, close-distance activities, outdoor activity time, reading habits, and education.

### Data Collection and Follow-Up

This study does not involve any intervention. All procedures are observational and consist of standardized ophthalmic examinations and questionnaire-based assessments conducted at baseline and at each annual follow-up visit. The following biological parameters were measured annually in children in the cohort: visual acuity, cycloplegic refraction, AL, ACD, CR, ocular position, fundus, height, weight, and other parameters.

First, visual acuity was assessed using the Early Treatment Diabetic Retinopathy Study visual acuity chart at a distance of 4 m, with the 1.0 line at eye level. Visual acuity was assessed monocularly, with one eye covered without applying pressure while the other eye was tested. Measurements were performed in a right-to-left sequence. The number of correctly identified letters was determined by reading optotypes from top to bottom.

Second, cycloplegic refraction was performed using 1% cyclopentolate hydrochloride. Initially, 1 drop of 0.4% oxybuprocaine hydrochloride (as topical anesthetic) was instilled. Following a 3-minute interval, 1% cyclopentolate hydrochloride eye drops were administered at 5- to 10-minute intervals for 3 consecutive doses. Pupillary diameter and light reflex were assessed 30 minutes after the final instillation. Complete cycloplegia was defined as pupillary dilation ≥6.0 mm and absence of pupillary light reflex (grade 0 on the standardized light reaction scale). Participants meeting these criteria underwent automated refraction using a calibrated autorefractor (Nidek ARK-1), with triplicate measurements obtained under mesopic conditions (3 cd/m²).

Third, ocular biometric parameters, including AL, CR, and ACD, are measured using an optical interferometric AL meter (AL-Scan, Nidek Co, Ltd). The AL to CR ratio is calculated as AL-to-CR=AL/mean CR. The device automatically obtained multiple measurements and reported averaged values.

Fourth, eye position was assessed using masking-demasking and alternating masking methods to screen for strabismus. The direction of ocular movement was assessed to determine whether the participant had strabismus or occult strabismus.

Data collection was completed annually within the specified time frame, with a total follow-up period of 3 years. To ensure patient adherence and maintain a high long-term follow-up rate, the following strategies were implemented: (1) collaborating institutions had extensive screening experience and a dedicated professional examination team; (2) a personalized refractive profile was established for each child in the cohort, along with a feedback mechanism for results; (3) volunteer certificates were awarded to children participating in the cohort study to enhance their engagement; and (4) an additional clinical coordinator was appointed to conduct detailed telephone communication with families before each annual follow-up, aiming to reduce lost follow-up rates. These measures also support the feasibility and acceptability of long-term follow-up in school-aged children and their families.

### Quality Control Measures and Data Management

The research team established standard operating procedures for the study and organized training programs, with records maintained in the project management files. To ensure that study personnel are adequately qualified to perform specific clinical research tasks, all involved staff must complete the following training before initiation of the project: (1) study protocol; (2) ophthalmic examination standard operating procedures, including protocols for cycloplegic refraction, visual acuity assessment, AL measurement, ACD, and other biometric parameter measurements; and (3) electronic database use. Training related to the project will be ongoing throughout the study, with the principal investigator and project coordinator adding content as needed.

The purpose of this study is to propose data management methods based on the Smart Vision Information OPERA-MC Adolescent Vision Screening and Monitoring Management System. Through an electronic questionnaire, we collected basic information about patients, their families, and their environment. Automated refraction (Nidek ARK-1) and noncontact tonometry (Canon TX-20P; Canon Medical Systems) were digitally interfaced via the standardized HL7 protocol through networked medical device ports. Digital fundus photography images (Topcon TRC-50DX; Topcon Healthcare, Inc) were automatically transmitted and archived in digital imaging and communications in medicine format using picture archiving and communication system integration. Examination results were transmitted electronically for direct collection and storage without manual data entry. This process improved data accuracy and timeliness while reducing the likelihood of missing data. We will check the accuracy and completeness of the database storage results by sampling the original data and comparing them with the stored data. The collected data will be recorded in case report forms and uploaded to the electronic data capture system for centralized management.

### Statistical Analysis Plan

In this project, the basic statistical design plan was a prospective nested case-control study, as shown in Figure 2. Statistical analyses will be conducted according to prespecified research questions and outcomes. Analyses will include descriptive analyses, primary inferential analyses for incident myopia, and secondary analyses for longitudinal changes in ocular biometric parameters.

Descriptive analyses will summarize participants’ baseline characteristics and annual follow-up measurements, including refractive status and ocular biometric parameters. Continuous variables will be reported as means (SDs) or medians (IQRs), as appropriate, and categorical variables will be summarized as frequencies and proportions. The distribution of continuous variables will be assessed using graphical methods (eg, histograms and Q-Q plots) and the Shapiro-Wilk test.

The primary inferential analysis will evaluate the association between physiological hyperopia and incident myopia. A nested case-control approach will be applied, in which children who develop myopia during follow-up will be identified as cases and matched in a 1:1 ratio with controls selected from cohort members who remain nonmyopic at the same follow-up time point. Conditional logistic regression models will be used to estimate odds ratios and 95% CIs, adjusting for potential confounders, including age, sex, parental myopia, time spent in outdoor activities, and time spent on near-work activities.

**Figure 2. F2:**
[figure not shown]
The basic statistical design plan of the study.

Secondary analyses will examine longitudinal changes in ocular biometric parameters, including AL, ACD, CR, and the AL to CR ratio. These analyses will be performed using linear mixed-effects models to account for within-subject repeated measurements over time. Participants will be grouped according to baseline levels of physiological hyperopia, and sensitivity analyses will be conducted accordingly.

Sensitivity analyses will be performed by stratifying participants according to baseline physiological hyperopia levels (eg, age-specific categories) and by evaluating alternative analytic-eye definitions (right eye only vs both eyes using appropriate correlation structures).

All statistical analyses will be performed using SPSS (version 26.0; IBM Corp), RStudio (version 1.4; Posit PBC), and MATLAB (version 2021a; MathWorks Inc). A 2-sided *P*<.05 will be considered statistically significant.

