## Methods

### Objective

This study aims to explore the key influencing factors for children’s physiological hyperopia fading and myopia onset, as well as the protective mechanisms of physiological hyperopia against myopia.

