The nested case-control study is an innovative research method that combines elements of traditional case-control and cohort studies, and its validity has been demonstrated in multiple large-scale studies [15-17]. Nested case-control sampling enables efficient and focused comparison between children who develop myopia and those who remain nonmyopic at the same follow-up time point, thereby preserving the temporal sequence between exposure and outcome while minimizing selection bias. In addition, key exposures of interest—such as baseline hyperopic reserve and the rate of physiological hyperopia regression—are age dependent and time varying. Risk-set matching within the cohort facilitates appropriate control for age and follow-up time and supports robust multivariable modeling of detailed exposure profiles.

Case-control sampling is performed only when new cases of myopia are identified during follow-up. Each incident myopia case is matched in a 1:1 ratio with a control selected from cohort members who remain at risk at the same time point. Cross-sectional analyses conducted at each follow-up visit are intended solely for descriptive and exploratory purposes and do not constitute part of the primary inferential analyses.

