### Conclusions

This prospective nested case-control study investigates the dynamic changes and regression patterns of physiological hyperopia in school-aged children and evaluates the associations between ocular biometric parameters and the onset of myopia. The findings are expected to support standardized myopia screening, inform clinical interventions, and provide evidence-based guidance for government policies on myopia prevention and control in young children.

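### Drivers of hyperopia fading are a stated aim, but change in refraction is no listed outcome or model response, and the primary odds ratio cannot by itself show protection

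*Protocol article*

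**What the plan says.** The Objective section of the protocol article names the factors behind "physiological hyperopia fading and myopia onset, as well as the protective mechanisms of physiological hyperopia against myopia". The last paragraph of the Introduction repeats regression of hyperopia as a target, and the Conclusions say the study "investigates the dynamic changes and regression patterns of physiological hyperopia in school-aged children".

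The planned outcomes and analyses are these:

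- **Primary outcome.** Incident myopia, with a cut-off on SER: "Myopia is defined as a spherical equivalent refraction (sphere +1/2 cylinder) of ≤−0.50 D in either eye under cycloplegia".
- **Secondary outcomes.** Prevalence of myopia, and annual change in axial length (AL), anterior chamber depth (ACD), corneal radius (CR) and AL/CR. Change in SER is not listed.
- **Primary analysis.** "The primary inferential analysis will evaluate the association between physiological hyperopia and incident myopia". It uses 1:1 risk-set matching: "Conditional logistic regression models will be used to estimate odds ratios and 95% CIs, adjusting for potential confounders". The named confounders include parental myopia, outdoor time and near work.
- **Secondary models.** "Secondary analyses will examine longitudinal changes in ocular biometric parameters, including AL, ACD, CR, and the AL to CR ratio". These are linear mixed models, with children grouped by baseline hyperopia.
- **Refraction over time.** Study Design assigns it to descriptive cohort-level work. The same section also lists exposures "such as baseline hyperopic reserve and the rate of physiological hyperopia regression".

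**The concern.** There are two linked problems.

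First, fading of hyperopia is change in SER. An aim to find its drivers needs SER change as a response, with the candidate drivers as explanatory terms. The plan has no such model. Outdoor time, near work and parental myopia are named in one model only, where the outcome is incident myopia and they serve as adjustment terms.

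Second, exposure and outcome in the primary analysis are the same quantity at two times. A child who starts closer to −0.50 D reaches it sooner at any common rate of change. A low odds ratio for baseline hyperopia is therefore expected whether or not hyperopia slows progression. If that odds ratio is read as protection, the study's headline and the policy guidance built on it would claim more than the analysis can show.

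**Working it through.** **Step 1. Match the aim to the outcomes and models.**

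| Quantity | Listed outcome | Response in an inferential model | Other use |
|---|---|---|---|
| Incident myopia | primary | conditional logistic | – |
| AL, ACD, CR, AL/CR change | secondary | linear mixed | – |
| SER change (fading) | no | no | described; rate of regression as exposure |

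SER is measured at every annual visit (Examinations; Data Collection and Follow-Up), so the data for the missing row will exist.

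**Step 2. The document's own gradient.** The plan gives no figure for its primary association. Anticipated Findings cites a 5-year cohort with incidence 4.4% for baseline SER above +2.00 D and nearly 92% for 0.00 to −0.50 D. Can one myopic shift, common to all children, produce both?

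Let the 5-year shift be normal with mean m and SD s. A child starting at b crosses if the shift is at least b + 0.50. Assume group midpoints of −0.25 D and h. Then:

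- s = (h + 0.25) / (1.405 + 1.706), where 1.405 and 1.706 are the normal quantiles for 0.92 and 0.956
- m = 0.25 + 1.405 × s

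For h = 2.25: s = 2.50/3.111 = 0.80 and m = 1.38 D. For h = 3.00: s = 3.25/3.111 = 1.04 and m = 1.72 D. Both cited incidences are reproduced with no slower progression in hyperopic children.

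**Step 3. Simulate the planned analysis.** From the document: 915 children (the stated minimum cohort), ages 6 to 9, three annual visits, myopia at SER ≤ −0.50 D, 1:1 risk-set controls, conditional logistic regression. Assumed: everything in the first four columns below, age matching within 0.5 year, adjustment for age only, and one SER value per child. There were 300 runs per row. The first six rows have progression independent of baseline.

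| Baseline SER mean/SD (D) | Yearly myopic shift (D) | Between-child slope SD (D) | Visit SD (D) | 3-year incidence | Pairs | Median OR per +1 D (2.5–97.5%) |
|---|---|---|---|---|---|---|
| 1.0/0.8 | 0.28 | 0.10 | 0.25 | 22% | 200 | 0.03 (0.01–0.06) |
| 1.0/0.8 | 0.30 | 0.20 | 0.30 | 28% | 251 | 0.10 (0.05–0.17) |
| 1.0/0.8 | 0.40 | 0.20 | 0.30 | 38% | 338 | 0.11 (0.06–0.17) |
| 1.2/0.9 | 0.50 | 0.30 | 0.30 | 43% | 380 | 0.20 (0.13–0.25) |
| 1.0/0.8 | 0.40 | 0.40 | 0.50 | 43% | 384 | 0.31 (0.23–0.40) |
| as row 2, plus 0.2 D measurement error | | | | 29% | 254 | 0.13 (0.07–0.21) |
| as row 2, more hyperopic **faster** by 0.10 D/year per D | | | | 26% | 227 | 0.20 (0.12–0.29) |
| as row 2, more hyperopic **slower** by 0.10 D/year per D | | | | 31% | 278 | 0.06 (0.02–0.10) |

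The odds ratio was significant at two-sided 0.05 in 100% of runs in every row. The value does not discriminate either: 0.20 arises both with no effect on progression (row 4) and with faster progression (row 7).

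**Step 4. Check the alternative response.** When annual SER change was regressed on baseline SER, rows 1 to 5 gave a mean slope of about 0.00 D/year per D and 4% to 6% rejections. Faster and slower progression gave −0.10 and +0.10. With 0.2 D measurement error (row 6), however, the naive regression gave −0.022 and falsely rejected in 45% of runs, which is regression to the mean. In a further check at 0.20 D error, fitted slopes that included the baseline visit falsely rejected in 55% of null runs, against about 5% when slopes used post-baseline visits only.

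**The case against.** Several counter-arguments carry weight.

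- **Rank of the aim.** Study Design says the main scientific objective is the transition to incident myopia, and the primary outcome and model fit it. That fading is named first in the Objective is only word order, so it should not be called the leading aim. It is still a stated aim, and description alone does not identify factors.
- **Other uses of refraction.** A reader might infer that refraction enters inference only as baseline SER. The documents do not support this, because Study Design also names rate of regression as an exposure. That does not fill the gap: it is still not a response, and crossing −0.50 D is itself regression.
- **Planned axial models.** A reader might infer that the study can offer nothing but a distance-to-threshold effect. That is too strong. The AL and AL/CR mixed models by baseline hyperopia group are off the SER scale and can speak to protection. They are secondary, however, are not presented as that test, and name no drivers of fading.
- **Validity of the odds ratio.** A reader might infer that the primary result is a false positive. It is not. Children further from the threshold do become myopic later, and Anticipated Findings speaks of hyperopia as a possible risk marker.
- **Existing caveats.** Limitations concedes that causality cannot be proven. But that caveat concerns observational design and residual confounding, which is a different problem. Anticipated Findings also states outright that hyperopia protects, and claims a firm basis for causal conclusions.
- **Condensed article.** Figure 2 is not shown and a fuller plan may exist. Still, the article does list its outcomes and model responses, and those lists do not cover its stated aim.

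**Conclusion.** The point holds in this form: as written, the plan cannot answer inferentially what drives hyperopia fading, and the primary odds ratio for baseline hyperopia cannot by itself show protection. With no effect of baseline on progression, that odds ratio is about 0.03 to 0.31 per +1 D. It remains below 1 when hyperopic children progress faster or slower.

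The SER distributions and progression rates are assumptions, so the size is a wide range; the direction was the same in every scenario. No effect here means no effect on the rate of refractive change. The primary analysis stands as risk prediction. Severity: should-fix.

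**What to change.** 1. Add annual change in cycloplegic SER to the secondary outcomes.
2. Fit a linear mixed model for SER with random child intercept and slope, including outdoor time, near work and parental myopia, each by time.
3. Report the incident-myopia odds ratio as risk prediction, and soften the protection and causal wording in Anticipated Findings to match.
4. Base any statement on protection on the AL and AL/CR mixed models by baseline hyperopia group, and on SER change analysed so that baseline measurement error does not bias it. Examples are the intercept–slope covariance of the mixed model, or slopes from post-baseline visits only. Do not use a naive regression of SER change on observed baseline.

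The cost is one more model and more cautious wording. No new measurement is needed, and the article says analysis begins only after data collection ends.
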